### Endpoints

#### *Primary endpoint*

The primary endpoint is the change in mean Hb concentration at month 12 of follow-up and anaemia prevalence one year after the initial preventive treatment.

#### *Secondary endpoints:*

1. Change in mean Hb concentration at month 4 and 8 of follow-up.

2. Prevalence of asymptomatic and clinical malaria at baseline and one year after enrolment.

3. Prevalence of *pf*DHFR and *pf*DHPS gene mutations at baseline and at month 12 follow-up.

4. Clinical (severe) malaria incidence and parasitaemia at month 4, 8 and 12.

5. Percentages of acute and severe malnutrition at month 0, 4, 8, 12 through weight/height and height/age z-scores, and skin folds.

6. School achievement at the end of follow-up and school attendance.

7. Prevalence and risk of environmental and host-related predictors for malaria (re)infections.

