#### *Secondary objectives*

Secondarily, in the same study population, the purpose of the study is to:

1. Determine the prevalence of SP resistance markers at baseline and at month 12 follow-up;.

2. Compare the efficacy and safety of SP versus SP-PQ.

3. Assess the impact of antimalarial IPTsc on malaria incidence and severity.

4. Evaluate the impact of IPTsc on the nutritional status of schoolchildren.

5. Evaluate the effect of antimalarial IPTsc on school performance.

6. Identify the potential environmental and host-related predictors of malaria (re)infections.

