### Patient selection and withdrawal

#### *Inclusion criteria for initial treatment*

In order to be eligible, children should satisfy all of the following criteria:

1. Male and female primary school children.

2. Anticipated local residence for the study duration.

3. Signed or thumb-printed informed consent by the parents or guardians and witnessed by an impartial witness (whenever parents/guardians are illiterate).

4. Informed consent for children 12-years-old or older.

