#### *Exclusion criteria*

Participants with at least one of the following criteria are excluded:

1. Children of the sixth primary school year.

2. Participation in any other investigational drug study (antimalarial or others) during the previous 30 days.

3. Known or suspected hypersensitivity or serious adverse events (AE) to the study drugs.

4. Malaria symptoms at baseline irrespective of the severity [see Additional file 1].

5. Febrile conditions caused by diseases other than malaria at the first visit.

6. Decompensated anaemia.

7. Illness or conditions, such as hematologic, cardiac, renal, hepatic diseases, which in the judgement of the investigators would place the subject at undue risk or interfere with the results of the study, including known glucose-6-phosphate dehydrogenase deficiency and sickle cell.

8. Body weight <14 kg.

9. Children with major chronic infectious diseases (HIV, tuberculosis, and so on).

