#### *Piperaquine*

PQ is not approved as a single entity. A fixed dose combination of PQ with dihydroartemisinin (DHA) was approved by the European Medicines Agency and marketed as Eurartesim for the treatment of uncomplicated malaria in children and infants of six months or older. The exact mechanism of action of PQ is unknown. PQ likely mirrors its closest structural analogue chloroquine. Chloroquine binds to toxic haeme (derived from the patient’s haemoglobin) within the parasite and prevents its detoxification. The Cmax and the AUC0-24 of PQ is 179 nm/ml and 1.679 ng/ml*h, respectively. The elimination half-life of PQ is around 20 days for paediatric patients. Due to its slow elimination, PQ may accumulate in plasma after multiple doses. In healthy volunteers, PQ exposure is increased approximately three-fold when administered with a high fat/high calorie meal. In combination curative treatment with DHA, PQ is safe and efficacious at 60 to 73.9 mg/kg dose in three daily doses against uncomplicated *P. falciparum* malaria [29,30]. However, because participants in this trial are healthy individuals, the parasite carriage is expected to be low. Taking account of the ED90 of PQ at 1.68 ± 0.210 mg/kg/day for *P. berghei* K-173, its CT100 of 42 hours and the long elimination half-life [31], PQ 320 mg tablets manufactured by Sigma Tau will be used at two treatment doses of 16 to 24 mg/kg body weight at 24-hour intervals (in combination with SP) as follows: 1 tablet for weigh 15 to 19 kg, 1.5 tablets for 20 to 29 kg, 2 tablets for 30 to 39 kg, and 2.5 tablets for 40 kg or more. The treatment will be administered with water under fasting conditions.

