## Abbreviations

AE: Adverse events; CRF: Case report form; DHA: Dihydroartemisinin; DHFR: Dihydrofolate reductase; DHPS: Dihydropteroate synthase; ELISA: Enzyme-linked immunosorbent assay; FACS: Fluorescence activated cell sorting; GCP: Good Clinical Practice; H/A: Height for age; ICH: International Conference on Harmonisation; IPT: Intermittent preventive treatment; IPTc: Intermittent preventive treatment in children; IPTi: Intermittent preventive treatment in infancy; IPTp: Intermittent preventive treatment in pregnancy; IPTsc: Intermittent preventive treatment in schoolchildren; LIC: Low income countries; MIC: Minimal inhibitory concentration; PCR: Polymerase chain reaction; PQ: Piperaquine; RCT: Randomised controlled trial; RR: Relative risk; SAE: Serious adverse events; SP: Sulfadoxine-pyrimethamine; SP-PQ: Sulfadoxine-pyrimethamine plus piperaquine; SSA: Sub Saharan Africa; STH: Soil transmitted helminths; W/H: Weight for height.

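### Secondary endpoint 5 measures acute malnutrition in schoolchildren with an age-free index (weight-for-height) and with one that contains no weight (height-for-age); BMI-for-age, with stunting reported separately, fits better

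*Protocol article*

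**What the plan says.** Under Secondary endpoints, item 5 of the protocol article reads "Percentages of acute and severe malnutrition at month 0, 4, 8, 12 through weight/height and height/age z-scores, and skin folds". The abbreviations list expands the first index ("W/H: Weight for height") and gives height for age as the second. Item 5 is the listed endpoint that answers secondary objective 4, "Evaluate the impact of IPTsc on the nutritional status of schoolchildren".

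The eligibility criteria describe the children to be scored. They are "Male and female primary school children", with no lower or upper age limit. The exclusions include "Children of the sixth primary school year" and "Body weight <14 kg". One inclusion criterion is "Informed consent for children 12-years-old or older", so such children are expected. The piperaquine weight bands end with "2 tablets for 30 to 39 kg, and 2.5 tablets for 40 kg or more".

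The article gives no growth reference, no z-score cut-off, and no age or height distribution. It does not say which index defines which category of malnutrition.

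**The concern.** There are two separate problems, and both lie in the endpoint's own wording.

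**Label and index do not match.** Acute malnutrition is a deficit of weight relative to body size. Height-for-age uses only height and age and describes growth accumulated over years. It is a measure of stunting, yet the endpoint names no stunting or chronic category.

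**The remaining z-score does not suit the age range.** Weight-for-height compares a child with others of the same height, whatever their age. From school age, and above all near puberty, the weight expected at a given height depends on age. Two children of equal height and weight but several years apart in age get the same score. A weight-for-height reference may also end at some height, beyond which no score exists.

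At stake is the answer to secondary objective 4. If scores are missing above a height limit, the acute-malnutrition percentage comes from the shorter and younger children, a selection on a variable that is itself tied to nutrition. Children also grow past the limit, so the percentages at months 0, 4, 8 and 12 would not describe the same children.

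**Working it through.** The article gives no prevalence, cut-off or power for this endpoint, so there is no figure of its own to reproduce. The check has two parts.

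**1. What each listed measure uses**

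| Measure | Weight | Height | Age | Can it show acute malnutrition? |
|---|---|---|---|---|
| Weight-for-height z | yes | yes | no | yes, but without regard to age |
| Height-for-age z | no | yes | yes | no; it shows stunting |
| Skin folds | no | no | no | it bears on fatness, but it is not listed as a z-score and no category is tied to it |
| BMI-for-age z (not listed) | yes | yes | yes | yes, as thinness |

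Of the two z-scores in the endpoint, only weight-for-height can define acute malnutrition. This step needs no outside figure.

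**2. How many children might have no weight-for-height score**

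The documents give neither the reference nor the heights, so every input here is an assumption:
- height ceiling of the reference: 120, 137 or 145 cm;
- mean age by school year 1 to 5: 6.5, 7.5, 8.5, 9.5, 10.5 years (on-age) or 7.5, 8.75, 10, 11.25, 12.5 years (over-age);
- median height at 6.5 years: 108, 112 or 117 cm; growth 5.3 cm a year; SD 6 cm within a school year; equal class sizes.

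Formula: the share above ceiling C is the mean over the five school years of 1 − Φ((C − [h + 5.3 × (age − 6.5)])/6), where h is the median height at 6.5 years.

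Worked case (on-age, h = 112, C = 120): the mean heights are 112, 117.3, 122.6, 127.9 and 133.2 cm. The shares above 120 cm are 0.091, 0.326, 0.668, 0.906 and 0.986. Their mean is 2.977/5 = 0.60.

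Share above the ceiling at baseline:

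| Ages | Median height at 6.5 y | 120 cm | 137 cm | 145 cm |
|---|---|---|---|---|
| on-age | 108 cm | 45% | 2% | 0% |
| on-age | 112 cm | 60% | 7% | 1% |
| on-age | 117 cm | 77% | 18% | 3% |
| over-age | 108 cm | 70% | 20% | 4% |
| over-age | 112 cm | 81% | 31% | 11% |
| over-age | 117 cm | 92% | 46% | 22% |

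**Drift during follow-up.** In the worked case, 12 months add 5.3 cm to each mean height. The shares become 0.326, 0.668, 0.906, 0.986 and 0.999, with mean 3.885/5 = 0.78. The unscored share rises from 60% to 78% between month 0 and month 12.

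**Cross-check with the dosing bands.** At 120 cm a child of 30 kg has a BMI of 30/1.2² = 20.8, and a child of 40 kg has 40/1.2² = 27.8. Children in the two upper bands would therefore mostly be taller than 120 cm. The bands do not say how many children fall in them.

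**The case against.** The strongest counter-argument is that the size of the loss is unknown. A reader might infer that weight-for-height cannot be scored for most of these children, or turn an assumed percentage of the planned 616 into a head count. The documents support neither. The ceiling is not stated, no heights are given, and under the assumptions above the unscored share is below half in every scenario with a ceiling of 137 or 145 cm. The consent criterion and the weight bands show that older and heavier children may be enrolled, not how many. This part of the objection stands, so the loss can only be stated conditionally.

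A second inference would be that secondary objective 4 rests entirely on a selected subset. It does not. Skin folds are listed for the same visits, height-for-age remains for children above any ceiling, and the objective concerns nutritional status in general. This also stands.

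Third, the wording does not force the reading that height-for-age defines acute malnutrition, since severity could be a grade on either index. That is fair, but it does not repair the endpoint. Height-for-age then still serves a category that the endpoint does not name, and weight-for-height still carries acute malnutrition alone.

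Fourth, an article may leave the growth reference and cut-offs to the full protocol or the analysis plan. That is true, and their absence is not the point made here. The choice of indices is fixed in the endpoint itself. A later choice of reference could remove the ceiling, but it would not make weight-for-height depend on age or give height-for-age a weight component.

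**Conclusion.** The point holds in a limited form. Without any outside figure, height-for-age cannot give a percentage of acute malnutrition, and the endpoint provides no stunting category for it. The only z-score left for acute malnutrition ignores age in a population with no age limit that includes children of 12 or older.

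The loss of scores is a conditional risk. Across the assumed height scenarios it runs from 0% to 92%, and it depends mainly on the reference ceiling. If there is a loss, it is selective on height and increases over the 12 months.

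The consequence is confined to one secondary endpoint. The primary haemoglobin endpoint, the sample size and the main model are not affected.

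**What to change.** In secondary endpoint 5, replace the weight/height z-score by the BMI-for-age z-score for all children, reported as the percentages with thinness and severe thinness. Report the height-for-age z-score separately as stunting. Skin folds can stay as a supporting measure. Name the growth reference and confirm that it covers the ages enrolled.

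The cost is a rewording of one endpoint and a different reference table in the analysis. No new measurement is needed, because the two z-scores already listed require weight, height and age. The small downside is less comparability with studies that report weight-for-height. Weight-for-height could be added as a descriptive result for the children whose height the reference covers, with their number stated at each visit.

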### Study hypothesis

Considering the facts that in our study area: (1) IPT of malaria provides substantial protection against anaemia and malaria in school children; (2) the level of SP resistance has no significant impact on the prophylactic efficacy [25]; and (3) SP-PQ is safe and as efficacious as SP, we hypothesize that antimalarial IPT with SP and SP-PQ will improve haemoglobin concentration, reduce anaemia prevalence, malaria incidence and parasitaemia, and improve nutritional status and school performance in school-aged children of DRCongo.

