### Design and sample size calculation

The study is an unblinded, randomised controlled trial, enrolling asymptomatic school children, either gender. At baseline, month four, and month eight, IPT with SP or SP-PQ is given. SP is administered as a single treatment dose. However, PQ is given as two doses with a 24-hour interval. IPT is administered at four month intervals in line with the long half-lives of the drugs and for compliance. Each treatment arm will be compared to the control group of untreated participants. Due to the prevalence of STH and schistosomiasis in the study area all participants are treated with albendazole or praziquantel according to the WHO guidelines [26]. Before the study, parents or guardians and children were informed about the objectives and the design of the study during organised meetings at schools.

Within each school, each schoolchild is randomly assigned to one of the two intervention groups or the control group as follows: IPT-SP, IPT-SP-PQ and no-treatment. Each study arm consists of one-third of all individuals.

To estimate the statistical power of our studies, we used an effect size of 0.56 g/dl mean Hb level improvement by the antimalarial IPT compared to the control treatment. This effect size was based upon a previous study.

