A previous study estimated the mean Hb concentration of 13.01 g/dl respectively in schoolchildren with IPT and 12.45 g/dl without [27]. The sample size of the study is all schoolchildren of two schools selected within the nearest schools to the regional hospital centre. The overall number of schoolchildren in the two schools is estimated to be 1,300 (650 in each school). By excluding 200 children of the sixth primary school year (100 per school), and accounting for 20% cancelation and 30% to 40% absenteeism, a realistic sample size of 616 individuals is reached for the complete IPT treatment schedule. Using this effect size and sample size, power estimates were performed by Monte Carlo simulation. In each run, a dataset was simulated assuming the within-subject variance and between-subject variability was 16, and putting in effect size to 1. The power was then estimated by fitting a linear mixed model to the data (Hb level versus treatment, time and time:treatment interaction) and testing the significance of the interaction term. The power is then equal to the fraction of times the interaction term was significant, using a significance level of 5%. A sample size of 616 offers 100% power to detect superiority between the control and the intervention groups. For the non-inferiority of SP versus SP-PQ, this sample size has over 91% power to detect a difference in effect less than 0.27 g/dl (<50%).

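### The only nutritional endpoint is a set of malnutrition percentages, although the continuous z-scores and skin folds behind them would answer objective 4 with more power

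*Protocol article*

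**What the plan says.** In the protocol article, item 4 of the Secondary objectives is to "Evaluate the impact of IPTsc on the nutritional status of schoolchildren". The Study hypothesis expects the preventive treatment to "improve nutritional status and school performance in school-aged children of DRCongo". Neither restricts the question to children below a malnutrition threshold.

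The endpoint list answers this objective in one place, item 5 of the Secondary endpoints: "Percentages of acute and severe malnutrition at month 0, 4, 8, 12 through weight/height and height/age z-scores, and skin folds". As worded, the outcome is the percentage, and the z-scores and skin folds are the route to it. No cut-off, expected prevalence, effect size or power is given for nutrition.

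Haemoglobin is treated differently. The Primary endpoint section names both the change in mean haemoglobin and the prevalence of anaemia, and the Statistical analysis plan section models haemoglobin as a continuous repeated measure. The sample size section also concerns haemoglobin only: "we used an effect size of 0.56 g/dl mean Hb level improvement by the antimalarial IPT compared to the control treatment".

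**The concern.** A z-score holds more information about a child's nutritional status than the label malnourished or not malnourished. Once arms are compared on the percentage alone, movement that leaves a child on the same side of the cut does not count, and a second, more extreme category leaves fewer cases still. If the treatment moves growth or weight by a modest amount across all children, a comparison of percentages has a good chance of missing it. Objective 4 could then be reported as showing no clear effect when the same measurements would have supported a sharper answer. The choice of variable is made in the endpoint definition itself, so it is not a modelling detail that a protocol would normally leave to the statistical analysis plan.

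**Working it through.** **Sample size.** The two schools have an estimated 1,300 children, less 200 in the sixth year. The section continues: "accounting for 20% cancelation and 30% to 40% absenteeism, a realistic sample size of 616 individuals is reached for the complete IPT treatment schedule". At 30% absenteeism, (1,300 - 200) x 0.80 x 0.70 = 616, which reproduces the stated figure exactly. At 40%, 1,100 x 0.80 x 0.60 = 528. Since "Each study arm consists of one-third of all individuals", there are 616/3, about 205 per arm, or 528/3 = 176 at the upper absenteeism figure.

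**Assumptions (not in the protocol).** Normally distributed z-score with SD 1; every treated child shifted up by 0.2 z; cut-off placed to give control-arm prevalences of 5%, 10%, 20% or 30%; two-sided 5% test. The protocol states the 5% but not the sidedness.

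**Mean z-score, unadjusted.** SE = sqrt(2/205) = 0.0988. Power = Phi(0.2/0.0988 - 1.96) = Phi(0.065) = 53%.

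**Mean z-score, baseline-adjusted (correlation 0.7).** SE = 0.0988 x sqrt(1 - 0.7^2) = 0.0705. Power = Phi(0.2/0.0705 - 1.96) = Phi(0.876) = 81%.

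**Percentage, unadjusted.** With control prevalence p1 and c = Phi^-1(p1), the treated prevalence is p2 = Phi(c - 0.2). Power is from the two-proportion z-test. For p1 = 5%: c = -1.645, p2 = Phi(-1.845) = 3.25%, difference 1.75 points, SE about 1.96 points, power Phi((1.75 - 1.96 x 1.96)/1.96) = Phi(-1.07) = 14%.

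| Control prevalence | Treated prevalence | Power on percentage | Power on mean | Share of power kept |
|---|---|---|---|---|
| 5% | 3.3% | 14% | 53% | 14/53 = 26% |
| 10% | 6.9% | 20% | 53% | 20/53 = 38% |
| 20% | 14.9% | 28% | 53% | 28/53 = 53% |
| 30% | 23.4% | 32% | 53% | 32/53 = 60% |

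At 15% prevalence the percentage gives 24% (24/53 = 45% kept). Without adjustment, then, more than half the power is lost up to a prevalence of about 15%, and less than half from about 20% upwards.

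**Same adjustment on both sides.** Simulation, 600 runs per cell, shift 0.2 z, correlation 0.7, baseline z-score as covariate in both models:

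| Control prevalence | Logistic regression on malnourished status | ANCOVA on z-score |
|---|---|---|
| 10% | 21% | 80% |
| 20% | 37% | 82% |
| 30% | 44% | 83% |

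The simulation error is about 2 points (sqrt(0.4 x 0.6/600) = 0.02). Adjusting for baseline helps the percentage only a little.

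**Sensitivity.**
- Shift of 0.3 z: 25-60% on the percentage against 86% on the mean, unadjusted.
- Shift of 0.1 z: 7-11% against 17%, unadjusted.
- Severe category, with the cut one SD further out and a shift of 0.2 z: about 5-16%.
- 176 per arm and a shift of 0.2 z: about 13-28% against 47% unadjusted and 75% adjusted.

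The mean is the stronger comparison in every uniform-shift scenario tried.

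**The case against.** **Analysis plan not shown.** This is a condensed article, its analysis section models haemoglobin only, and no test or power is claimed for nutrition. Nothing says the z-scores will be discarded, and skin folds carry no stated cut-off. The unseen plan may well analyse them as continuous. This limits how much harm can be presumed, but the declared endpoint would still be the percentage.

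**The percentage is a meaningful outcome.** The abstract gives prevention of anaemia and malnutrition as the rationale, and the percentage malnourished speaks to that directly. The primary endpoint also pairs a mean with a prevalence. This stands, and is why the percentages should be kept. It also shows that the trial reports both forms for anaemia but only one for nutrition.

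**The shift model favours the mean.** If benefit is concentrated in malnourished children, the loss is smaller. This stands too.

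**Stronger readings that the documents do not support:**
- A reader might infer that most of the power is lost whatever the prevalence. That depends on figures the protocol does not give and fails, unadjusted, at 20-30%.
- A reader might infer that malnutrition must be rare because the children are asymptomatic. That term refers to malaria. Nutritional status is not an exclusion criterion beyond weight below 14 kg, and the Discussion speaks of youngsters who fail to thrive.
- Setting the adjusted 81% against the unadjusted 14-32% suggests a gain of 49-67 points, but it credits the cut-off with a loss due partly to omitting the baseline. The like-for-like table is the fair comparison.
- It would be wrong to say that only children crossing the cut contribute. Item 5 is a prevalence at each visit, and every child is in the denominator.
- It would be wrong to say that objective 4 becomes unanswerable. The measurements remain available.

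**Conclusion.** The point holds as a cheap improvement to a secondary endpoint. Item 5 names only percentages where continuous measurements are taken, and under a uniform shift those measurements give the stronger test of objective 4. For 205 per arm and 0.2 z, the difference is about 14-32% against 53% unadjusted, and about 21-44% against 80-83% with baseline in both. These powers are illustrations resting on an assumed SD, shift, prevalence and correlation. They show the direction and likely order of the loss, not its value in this trial. The direction would be less certain only if the effect were confined to children near or below the cut.

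**What to change.** Reword item 5 so that the between-arm comparison is the difference in mean weight/height and height/age z-score, and in mean skin fold, at month 12, adjusted for the child's baseline value. Months 4 and 8 can be added through the linear mixed model already planned for haemoglobin, provided that anthropometry is taken at those visits. Item 5 implies that it is, but Table 1 has no anthropometry row and schedules clinical examination only at baseline and month 12, so this should be confirmed. The month-12 comparison needs only the baseline and month-12 values. Keep the percentages of malnourished children by arm and visit as supportive results.

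The cost is the wording of one endpoint and one further model per measure. No extra children are needed, and no extra measurements beyond those item 5 already lists. The downside is that a difference in mean z-score is less familiar to policy readers than a percentage, which is a further reason to leave the percentages in the report.
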